#### Interventions (weeks 9–19) {11a}

The BEAM and MoodMission App-based programs will be offered via mobile device (both are functional on Android and iOS platforms). Participants will be provided with a mobile device, if required.

##### The Building Emotional Awareness and Mental Health Program (Intervention Group)

The BEAM program was designed to promote intergenerational well-being through the treatment of maternal mental illness and preventing child mental health concerns, by integrating parenting and self-compassion skills with UP modules [16, 18]. The interrelated skills are designed to increase supportive parenting behaviors and promote maternal-child bonding to disrupt each of the theorized mechanisms of environmental risk transmission (e.g., positive emotional modelling, improved relationships, support for children’s distress, reduced conflict [15, 37]).

The BEAM program is a 10-week guided mental health and parenting program where participants move through modules with a cohort of other mothers experiencing depression and/or anxiety. Each week includes 10–30 min of psychoeducational video content, weekly mood tracking, a 1-hour weekly group telehealth session with content review and facilitated discussions in breakout rooms, access to an online forum to cultivate peer support, and assignments to practice key skills. The BEAM program content has been developed in collaboration with our PAB and the Family Dynamics team.

###### Clinical team

BEAM clinical coaches will consist of mental health therapists (completing a Master's or Doctoral degree in Clinical Psychology who are supervised by a registered clinical psychologist), parent coaches from Family Dynamics, and a peer coach. Parent coaches are mental health staff (trained paraprofessionals) from Family Dynamics. Peer coaches are mothers who recently completed a program targeting their own mental health needs and who have agreed to help promote maternal mental wellness [15]. Clinical coaches will lead/co-lead weekly group telehealth sessions, manage participant contact via email/phone, and participate in weekly supervision meetings with clinical psychologists. Parent and peer coaches will participate in weekly group telehealth sessions and engage with participants on the online community forum.

###### Psychoeducation

The BEAM program will include psychoeducational materials consisting of separate weekly videos on mental health and parenting skills. These videos will be approximately 5 to 15 min long each (totaling 10 to 30 min per week). Mental health videos will provide easily digestible information on emotion regulation strategies adapted from the UP, an evidence-based transdiagnostic treatment for depressive and anxiety disorders [16, 18], and will focus on self-compassion skills. Parenting skill videos will teach emotion-focused and behavior management strategies to help mothers understand and co-regulate their child’s challenging behaviors. Videos will also teach mothers how to prevent negative mother–child interactions and promote positive relationships.

###### Mood tracking

Brief weekly questionnaires on depression (Patient Health Questionnaire-2 Item; PHQ-2) [38], anxiety (Generalized Anxiety Disorder-2 Item; GAD-2) [39], parenting stress (modified version of the Parenting Stress Index; PSI-4) [40], and positive mood (modified version of the Positive and Negative Affect Scale; PANAS-2) [41] will be sent to participants. Scores for each questionnaire will be provided, allowing mothers to track their weekly scores. Mood tracking is shown to promote emotional understanding [42].

###### Weekly group telehealth sessions

Weekly group telehealth sessions will provide mothers with the opportunity to discuss program material with coaches and peers, ask questions, and gain a sense of community. There will be three telehealth groups with different schedules to accommodate as many mothers as possible.

###### Online community forum

An online community forum will provide mothers with the opportunity to reflect on learned skills from the BEAM weekly modules and access social support by connecting with other mothers in the program. This will be a confidential, closed forum overseen by peer and parent coaches. The forum will consist of open-ended discussions between participants, peer advice, and sharing of anecdotes/non-identifying photos of their wellness journey. Mothers will be able to ask parent and peer coaches mental health- and parenting-related questions.

##### MoodMission (Standard of Care Group)

The SOC arm will receive MoodMission, an App-based program effective in the treatment of moderate depression and anxiety in adults and increasing their well-being [27–30]. MoodMission uses an adaptive learning algorithm based on self-reported level of distress during prior engagement. Based on this algorithm, participants are provided with five targeted cognitive-behavioral therapy strategies to build self-efficacy. Compared to BEAM, this self-paced generalized service is not tailored to the complex needs faced by parents and lacks coaching, social support, and parenting skills development. MoodMission was chosen as the SOC because it has been rigorously studied using RCTs [27–30]. Those in the MoodMission group will work through program content on the App at their own pace.

#### Post-intervention questionnaires (weeks 19–21)

Mothers will be given 2 weeks to complete the post-intervention questionnaires via RedCap after the BEAM and MoodMission programs are complete (see Tables 1 and 2). Participants will be invited to complete these questionnaires regardless of program completion.

#### Follow-up questionnaires (weeks 32–34)

Approximately 6 months following program completion, mothers will be sent a series of follow-up questionnaires via RedCap (see Tables 1 and 2).

#### Compensation

Mothers will be compensated a total of $160/Canadian Dollars ($50 for enrollment [$25 for a psychodiagnostic mental health assessment and $25 for pre-intervention surveys], $50 for the post-intervention questionnaires, $25 for the follow-up questionnaires, $25 for participants who complete > 75% of the weekly surveys, and $10 for those who complete the post-intervention questionnaire within 1 week of distribution)^1^ Participants deemed ineligible after the psychodiagnostics mental health interview will be compensated with $25/Canadian Dollars.

### Criteria for discontinuing or modifying allocated interventions {11b}

Clinical coaches will receive an alert from REDCap [31] if suicidality items are endorsed during the pre-intervention, post-intervention, or follow-up surveys [i.e., endorsing “Thoughts that you would be better off dead or of hurting yourself in some way” on the PHQ-9 [35] or a 2 + on any items on the Depression Severity Index—Suicidality Subscale (DSI-SS) [43]] and/or during the psychodiagnostics mental health assessment. These alerts will prompt clinical coaches to take necessary steps to assess participant safety and provide appropriate intervention. The clinical team will consult on any instances of suicidality to determine whether it is in the participant’s best interest to continue in the study. Of those in the BEAM program, participants may have discontinued access to the online community forum and/or denied access to weekly group telehealth sessions if they repeatedly violate terms of use. Further, if a participant cannot maintain the confidentiality of others during weekly group telehealth sessions, they may be denied access. In the above case, participants will still have access to all psychoeducational materials on the BEAM app and will be invited to complete all questionnaires. Clinical coaches would also provide referrals to other clinicians and clinics, if appropriate.

### Strategies to improve adherence and intervention protocols {11c}

Once a mother is randomized, all efforts will be made to follow the participant for the study duration. A recent iteration of BEAM for mothers of children 18–36 months old had an 83.7% retention rate (16.3% lost to follow-up) [44]. First, mothers will be asked to confirm their availability for weekly group telehealth sessions on the eligibility screener and will participate in a Zoom orientation with a parent coach. Second, participants in the BEAM program will receive three weekly push notifications via the BEAM App as well as a weekly reminder via email. Engagement notifications contribute to increased mental health benefits of mHealth interventions [45]. Third, those in the BEAM program will also be contacted by their clinical coach if they have not attended a weekly telehealth group session. Fourth, compensation will be provided across study participation (see below) to encourage completion; participants will be encouraged to complete questionnaires regardless of program completion.

### Outcomes {12}

Pre-specified success criteria are identified in Table 3. All feasibility indicators will be dichotomized into success or revise. “Success” indicates the protocol can move forward with a larger RCT with no/little revisions required, while “revise” suggests changes are needed prior to proceeding.

**Table 3 Tab3:** Feasibility indicators

Feasibility	Indictor	Criteria for success

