### Trial Registration – Data Set {2b}

**Table Taba:** 

**Primary registry and trial identifying number**	ClinicalTrials.gov, NCT05398107
**Date of registration in primary registry**	31 May, 2022
**Primary Sponsor**	University of Manitoba
**Contact for public queries**	[name] [[contact]]
**Contact for scientific queries**	[name] University of Manitoba, Winnipeg, Manitoba, Canada
**Public title**	A Community Partnership with Family Dynamics to Examine the Building Emotional Awareness and Mental health (BEAM) Program for Mothers of Young Children
**Scientific titles**	The Building Emotional Awareness and Mental health (BEAM) Program Developed with a Community Partner for Mothers of Infants: Protocol for a Feasibility Randomized Controlled Trial
**Countries of recruitment**	Canada
**Health condition(s) or problem(s) studied**	Depression, Anxiety
**Interventions**	*Intervention*: Building Emotional Awareness and Mental health (BEAM) program
	*Comparator*: MoodMission
**Key inclusion and exclusion criteria**	*Age of eligibility for study:* ≥ 18 years old *Inclusion Criteria:* Identifies as a mother; Has a child 6–18 months old; Resides in Manitoba, Canada; has access to a cellular network; > 9 on the Patient Health Questionnaire-9 and/or Generalized Anxiety Disorder-7; Meets criteria for a major depressive disorder and/or anxiety disorder on the Mini International Neuropsychiatric Interview (MINI); Completed the pre-intervention survey before randomization; Available to attend weekly telehealth sessions; Comfortable with English (spoken and written) *Exclusion Criteria*: Suicide attempt in the past year; Self-harm in the past 6 months; Clinically significant psychotic symptoms, posttraumatic stress disorder, or severe alcohol use disorder on the MINI which would interfere with the mother’s ability to attend and/or benefit from services.
**Study type**	Intervention
	*Allocation:* Randomized *Intervention Model*: Parallel Assignment *Masking*: Unblinded
	*Primary purpose*: Treatment
	Pilot and Feasibility
**Date of first enrolment**	February 2022
**Target Sample Size**	80
**Recruitment status**	Active, not recruiting
**Primary Outcomes**	1. Recruitment Rate 2. Retention Rate 3. Perceived Usefulness 4. Processing Time 5. Post-Intervention Questionnaire Completion Time 6. Follow-Up Questionnaire Time 7. Questionnaire Completion 8. Treatment Adherence 9. Safety
**Secondary Outcomes**	1. Treatment Response 2. Treatment Effect 3. Baseline Severity Moderation

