***Aim 1***		
Recruitment rate	Number of mothers per week recruited	Mean 2 participants/week
Retention rate	% of mothers with data at follow-up	> 80% of mothers with follow-up data
Perceived usefulness	Usefulness subscale of mHealth App Usability Questionnaire	Mean score of < 3
Processing time	Time from initial contact until study enrollment	Mean time is < 1 week
Post-intervention questionnaire completion time	Time to complete post-intervention questionnaires	Mean of < 60 min to complete
Follow-Up questionnaire completion time	Time to complete follow-up questionnaires	Mean of < 60 min to complete
Questionnaire completion	% of missing data among program completers	> 80% of data is present among mothers who completed follow-up
Treatment adherence	Logging onto BEAM App and/or attending weekly group telehealth session	Participation in > 50% of program weeks via logging onto BEAM App or attending weekly group telehealth session
Safety	Adverse events from the BEAM program or assessments	No adverse events reported

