***Aim 2***		
Treatment response	Comparison between groups	Significant group difference in primary clinical outcomes (depression and anxiety)
Treatment effect	Estimate of effect size and variance for future sample size calculations	Data on all relevant variables
Baseline severity moderation	Comparison of those with low versus high baseline scores on the PHQ-9 and GAD-7	Significant group difference

#### Aim 1

Back-end App data, collected via Google Analytics and Firebase, will be used to assess recommended mHealth engagement variables [46, 47]: (a) number of logins and sessions to the BEAM app, (b) number of forum posts, (c) time spent on the BEAM app and on the forum, (d) number of videos watched/time spent watching videos, and (e) number of weeks between first and last engagement with the app. Weekly telehealth group session attendance (yes/no) will be compiled by the clinical team. Analytics and group attendance data will also be used to assess retention (number of weeks completed) and completion (participating in > 50% of program weeks by either logging onto the BEAM app or attending the weekly group telehealth session). Finally, the mHealth App Usability Questionnaire (MAUQ) [48] will assess participants’ views on the BEAM program.

#### Aim 2

Data on maternal depression (PHQ-9) and anxiety (GAD-7) will be used to estimate effect size for a future large-scale RCT and to assess preliminary mean change in variables of interest across assessment timepoints. The PHQ-9 includes [35] nine items which will ask mothers the severity of their depressive symptoms during the past 2 weeks. The PHQ-9 has high internal consistency (*α* = 0.88) [49]. Anxiety symptom severity will be assessed using the GAD-7, a seven-item measure which will ask mothers their degree of anxiety symptoms over the past 2 weeks. The GAD-7 has excellent internal consistency (*α* = 0.92) [36]. Items on both scales are scored on a 4-point Likert scale ranging from 0 (“Not at all”) to 3 (“Nearly every day”) where higher summative scores suggest more problematic symptoms.

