### Sample size {14}

As this is a pilot and feasibility study, a sample size calculation is not appropriate. However, our target sample size of 30 participants per group is consistent with prior recommendations and will provide data to sufficiently establish BEAM feasibility [62, 63]. Accounting for a conservative 30% attrition rate [24], we will recruit an additional 10 participants per group (*N* = 80). With an estimated BEAM sample size of 40 mothers, we aim to achieve questionnaire completion and retention rates of 80% to within a 95% confidence interval of ± 12.4% as well as a treatment adherence rate of 50% to within a 95% confidence interval of ± 15.5%.

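### Table 3 makes non-significance on two Aim 2 tests a reason to mark the protocol 'revise', although the trial was not powered for either test

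*Protocol article*

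**What the plan says.** Outcomes {12} introduces Table 3, headed as feasibility indicators, with this rule: "All feasibility indicators will be dichotomized into success or revise". A 'success' verdict "indicates the protocol can move forward with a larger RCT with no/little revisions required"; a 'revise' verdict "suggests changes are needed prior to proceeding".

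Table 3 has twelve rows. Nine belong to Aim 1 and match the registered primary outcomes ("1. Recruitment Rate 2. Retention Rate 3. Perceived Usefulness 4. Processing Time" and five more). Three belong to Aim 2 and are registered as secondary: "1. Treatment Response 2. Treatment Effect 3. Baseline Severity Moderation".

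The Aim 2 criteria are:
- **Treatment response:** a significant difference between groups on depression and anxiety.
- **Treatment effect:** data available on all relevant variables, so that effect size and variance can be estimated.
- **Baseline severity moderation:** a significant group difference, for a row described as "Comparison of those with low versus high baseline scores on the PHQ-9 and GAD-7".

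Sample size {14} says that a sample size calculation is not appropriate for a pilot. It takes 30 per group from prior recommendations and recruits 40 per group to allow for attrition. The only precision it states is for three Aim 1 proportions in the BEAM arm ("we aim to achieve questionnaire completion and retention rates of 80"% and an adherence rate of 50%). Statistical methods {20a} sets alpha at 0.05, describes the Aim 2 tests as preliminary, and promises means with 95% confidence intervals.

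**The concern.** The rule covers every row of Table 3, so a p-value above 0.05 on treatment response or on moderation returns 'revise', which is worded as a need to change the protocol before the larger RCT. A pilot of this size is not built to deliver significance on either test. A non-significant result would then say more about the sample size than about whether BEAM can be delivered and studied with the community partner.

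The moderation row has a further problem. If BEAM works equally well at low and high baseline severity, there is no moderation to find. That would be no defect of the protocol, yet the row would read 'revise'.

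At stake is the readiness conclusion that the trial exists to give. The rule also works against Aim 2 itself, whose stated purpose includes estimating effect size and variance for planning.

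**Working it through.** **Inputs from the protocol article.** Alpha is 0.05 (Statistical methods {20a}); sidedness is not stated and two-sided is assumed. There are 30 per group as the analysis target and 40 per group recruited, allocated 1:1 (Sample size {14}). No effect size, SD or power is given, so the effect sizes below are assumptions shown as a range.

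**The plan's own figures.** The half-width is 1.96 × √(p(1 − p)/n) with n = 40.
- p = 0.80: 1.96 × √(0.16/40) = 12.4 points.
- p = 0.50: 1.96 × √(0.25/40) = 15.5 points.

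Both stated values reproduce. They concern Aim 1 proportions and say nothing about the Aim 2 tests.

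**Treatment response, one outcome.** Power ≈ Φ(d × √(n/2) − 1.96), where d is the standardised group difference and n the number per group.

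| Assumed d | n = 30 | n = 40 |
|---|---|---|
| 0.3 | Φ(1.16 − 1.96) = 0.21 | Φ(1.34 − 1.96) = 0.27 |
| 0.5 | Φ(1.94 − 1.96) = 0.49 | Φ(2.24 − 1.96) = 0.61 |
| 0.8 | Φ(3.10 − 1.96) = 0.87 | Φ(3.58 − 1.96) = 0.95 |

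With the t distribution, the d = 0.5 row becomes 0.48 and 0.60. Table 3 does not say whether both outcomes must be significant or either is enough. If both are needed, power is no higher than in the table. If either is enough, with equal effects and independent outcomes (a favourable assumption), power at d = 0.5 is 1 − (1 − 0.49)² = 0.74 with 30 per group and 1 − (1 − 0.61)² = 0.85 with 40.

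**Baseline severity moderation.** Assume a half split into low and high severity, so each of the four cells holds n/2 mothers. The standard error of the difference of differences, in SD units, is √(4/(n/2)).
- n = 30: SE = √(4/15) = 0.516.
- n = 40: SE = √(4/20) = 0.447.

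Power ≈ Φ(interaction/SE − 1.96).

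| Assumed interaction | n = 30 | n = 40 |
|---|---|---|
| 0.5 SD | Φ(0.97 − 1.96) = 0.16 | Φ(1.12 − 1.96) = 0.20 |
| 0.8 SD | Φ(1.55 − 1.96) = 0.34 | Φ(1.79 − 1.96) = 0.43 |

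With no true interaction, the row is met only by chance, at about the 5% level.

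**Effect of the planned model.** The plan specifies a longitudinal analysis of covariance. If adjustment for baseline removes a share r² of the variance, d becomes d/√(1 − r²). At an assumed r = 0.5, d = 0.5 becomes 0.5/√0.75 = 0.577, and power rises to Φ(2.24 − 1.96) = 0.61 with 30 per group and Φ(2.58 − 1.96) = 0.73 with 40. For the 0.5 SD interaction it rises to Φ(1.12 − 1.96) = 0.20 and Φ(1.29 − 1.96) = 0.25. The gain is real, but the moderation row still fails most of the time.

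**The case against.** The best defence is that the Aim 2 rows were never meant to decide progression. Objectives {7} names feasibility indicators only under Aim 1, the registry entry lists the Aim 2 rows as secondary, and Statistical methods {20a} calls the tests preliminary. This suggests that the team would not hold back a larger trial over a p-value. It does not remove the point: Table 3 lists these rows as feasibility indicators with success criteria, and Outcomes {12} applies the verdict to all indicators.

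Power also depends on assumed effects. At d = 0.8 the treatment response row would usually be met, and a moderation analysis on the continuous baseline score could do better than a half split. That is why a range is given. Neither argument makes significance a measure of feasibility.

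A reader might infer more, in three ways that the document does not support.
- **That a split set of verdicts is contradictory,** telling the team both to proceed and to stop. Each verdict attaches to its own indicator and both lead on to a larger RCT. Mixed verdicts read naturally as: change what was flagged, then proceed. The article does not spell this out, which is a gap in wording.
- **That a mixed result has a known, high probability.** Such figures need an assumed uniform pass rate. For nine rows at 90% each, the chance of a mixed set is 0.61 under independence (1 − 0.9⁹, since the chance that all nine fail is negligible) but 0.38 at a latent correlation of 0.5. The document fixes neither input.
- **That retention, adherence and questionnaire completion should decide,** because the trial was sized on them. It was not: their precision was worked out at a sample size already chosen. Objectives {7} gives recruitment, retention and perceived usefulness as its examples.

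**Conclusion.** The point holds for the Aim 2 rows. As written, Outcomes {12} and Table 3 turn non-significance on treatment response or baseline severity moderation into 'revise', in a trial with no power calculation. With 30 to 40 mothers per group, power is about 0.48 to 0.61 for one outcome at an assumed d of 0.5 (0.21 to 0.27 at 0.3), and about 0.16 to 0.20 for moderation at an assumed 0.5 SD interaction on a half split. These figures assume a two-sided 5% test with no gain from baseline adjustment. Adjustment at r = 0.5 raises them to 0.61 to 0.73 at d = 0.5 and 0.20 to 0.25 for moderation.

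A feasible protocol would thus often be marked 'revise' for reasons unrelated to feasibility. The conclusion on moderation does not depend on the power figures, because absence of moderation is no evidence against feasibility.

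For the Aim 1 rows, the missing statement on how to read split verdicts is minor and needs only a clarification. It does not justify re-ranking the outcomes.

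**What to change.** 1. Take the three Aim 2 rows out of the success/revise scheme in Table 3. Report treatment response, treatment effect and baseline severity moderation as estimates with 95% confidence intervals, and report the variance needed for planning. This fits the estimation purpose in Objectives {7} and the reporting already promised in Statistical methods {20a}.
2. Add one dated sentence to Outcomes {12}: a 'revise' on an Aim 1 indicator means that the component it flags is changed before the larger RCT. Recruitment ended in March 2022, primary outcome collection was expected to finish in December 2022, this version is dated February 2023, and the analysts are not blinded. If outcome data had been examined before the sentence is added, label it post hoc.
3. Keep the nine registered primary outcomes, and do not single out three as deciding. Removing primary status from the other six after recruitment has ended would itself invite the charge of choosing outcomes late.

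The cost is a text edit, with no new data or analysis. The small downside is that the trial makes no significance-based claim of success for Aim 2.
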